### Sample Sizes

According to research design standards [65], a minimum of 3 replications are recommended in a SCED study (substudy 1). However, to achieve sufficient power for randomization tests, a higher number of potential randomizations is recommended [66]. The number of randomizations is influenced by both the number of participants and the number of possible starting points; hence, guided by Levin et al [67], we chose 6 participants in each group.

For substudy 2, we based our power analysis on potential differences in cognitive bias and interoception between cases and healthy controls on a previous similar study on cognitive bias in children and adolescents [40] and studies on interoceptive accuracy in adults with functional disorders [68-69]. Based on these study findings, calculations show that in order to detect a minimum effect size of 0.5 (Cohen *d*), 60 patients and 100 healthy controls are required for the cognitive bias outcome, and a minimum of 51 patients and 51 healthy controls for the interoception outcome to achieve 80% power at an α level of .05. The subsequent analysis of the possible impact of treatment on these 2 factors is more explorative and therefore no a priori power calculation is provided. The same concerns the last study on parental factors (substudy 3) as possible effect moderators. However, here the sample size is the largest possible, comprised of parents from substudies 1 and 2.

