In line with this, cognitive behavioral therapy (CBT) is the treatment supported by the strongest evidence of effect [24-26], with its main focus on restructuring potential child symptom-related maladaptive cognitions, emotions, and behaviors, and often with parental involvement. Swedish studies have documented the efficacy of internet-delivered cognitive behavioral therapy (ICBT) aimed at children and adolescents with FAPDs and their parents [27-29]. The ICBT focuses especially on exposure exercises and parental management of their child or adolescent’s symptoms. By enabling the child or adolescent to manage symptoms in previously avoided situations and thereby minimizing the gastrointestinal-specific fear, the treatment reduces the proposed visceral hypersensitivity, which over time leads to fewer abdominal symptoms.

Still, a proportion of the young patients do not improve from ICBT as the number needed to treat has been reported to be around 4, meaning approximately 4 patients must receive the treatment for 1 additional patient to experience adequate symptom relief [27,29]. Therefore, a deeper understanding of the mechanisms of change and the potential influence of additional modifiable factors on the treatment effect is required to improve treatment effects even more.

In the current study, we will evaluate translated versions of the Swedish ICBT for children and adolescents with FAPDs in a Danish context. The treatments target both children (aged 8-12 years) and adolescents (aged 13-17 years) and their parents, which provides a unique possibility to examine both child or adolescent and parental factors before and after treatment. The aims of the study are to (1) investigate the detailed trajectory of the effect of ICBT in children and adolescents with FAPDs, (2) explore potential illness-related cognitive biases and interoceptive accuracy in children and adolescents with FAPDs compared with healthy controls, and if these factors are changed after ICBT, and (3) explore if parental distress, illness worries, and behaviors may impact the child or adolescent’s treatment adherence and outcome.

This protocol article is reported following the SPIRIT (Standard Protocol Items Recommendations for Interventional Trials) guidelines [30].

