For both studies in substudy 2, we will perform parallel studies on healthy controls. The BY-GIS task was already tested in 96 healthy controls [38], and the interoception test setup will be performed in 60 healthy controls (all aged 8-17 years).

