### Data Analyses

In substudy 1, visual inspection analyses will be applied to demonstrate the effect of the intervention on all outcomes [71]. In addition, within-case effect size measurements will be calculated using Tau-U [72] and between-case effect sizes will be determined using hierarchical linear regression models to account for the serial dependency of data [73]. A randomization test will be applied to test differences in means for the baseline versus treatment, and baseline versus follow-up periods, respectively [74].

In substudy 2, participants’ descriptions reported in the recall phase of the BY-GIS task will be coded to their corresponding word or picture and category presented in the encoding phase (eg, picture-description “children and cake” coded as the birthday picture within the fun category). Coding for the first 20% of participants will be conducted by 2 independent raters ([name] and [name]). If the consensus rating exceeds 90%, 1 rater will code the remaining cases independently. A third and experienced rater ([name]) may be consulted to resolve potential disagreements. Baseline data will be analyzed descriptively and compared with (1) data from a healthy control group who performed the same experimental test [38], and (2) end-of-treatment data, exploring potential differences in the outcomes from the encoding, recall, and recognition phases using *t* tests or nonparametric tests, depending on data variability in the samples.

Baseline measures of interoceptive performance and metacognitive measures will be analyzed descriptively and compared with (1) measures from a healthy control group and (2) end-of-treatment measures, using *t* tests or nonparametric tests, depending on data variability in the samples.

In substudy 3, the potential moderation of parental factors on treatment adherence (number of completed modules) and main measure (gastrointestinal symptoms) for children or adolescents will be investigated using negative binomial regression and linear mixed models, respectively, adjusting for baseline parental distress, illness worries, and illness behavior, respectively.

In addition, the potential effect of treatment on these parental factors and all other child or adolescent measures will be analyzed using linear mixed regression models.

An experienced statistician will provide statistical support for all analyses.

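### The stated 80% power for 51 patients and 51 controls on interoception holds only for a one-sided test; two-sided it is about 71%, and about 78% at the planned 60 per group

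*Protocol article*

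**What the plan says.** The Sample Sizes section of the protocol article gives one set of inputs for both patient-control comparisons in substudy 2. The calculation is made "in order to detect a minimum effect size of 0.5" on the Cohen d scale and "to achieve 80% power at an α level of .05". For cognitive bias it concludes that "60 patients and 100 healthy controls are required for the cognitive bias outcome". For interoception it asks for "a minimum of 51 patients and 51 healthy controls for the interoception outcome to achieve 80% power". It does not say whether α is one-sided or two-sided.

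The planned numbers are given elsewhere. Study Design sets substudy 2 at 60 patients. The section on cognitive bias and interoception measures says that "the interoception test setup will be performed in 60 healthy controls" and that "The BY-GIS task was already tested in 96 healthy controls".

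The second aim in the Introduction is to "explore potential illness-related cognitive biases and interoceptive accuracy in children and adolescents with FAPDs compared with healthy controls". Data Analyses plans t tests or nonparametric tests of baseline measures against healthy controls, for both cognitive bias and interoception, and names no direction.

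**The concern.** With effect size, α and power all stated, the sample size for a two-group t test is fixed once sidedness is known. For d = 0.5 and two-sided α = .05 the familiar answer is 64 per group, so 51 stands out as too small. It is the size that a one-sided test would give.

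Nothing in the article supports a one-sided test. The aim is exploratory. The sample size paragraph speaks of potential differences, and the analysis section names no direction. The Discussion refers to inaccurate interoception in one place, and to altered accuracy and a possible general hypersensitivity in another. No direction is set for any of the task's outcomes (threshold, slope, reaction time, confidence).

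What is at stake is how a null interoception result is read. A reader who takes 51 per group as the 80% minimum would think that 60 per group leaves room to spare, when on a two-sided test it falls slightly below 80%.

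**Working it through.** **Inputs.** d = 0.5, α = .05, target power 80%, 51 versus 51 (Sample Sizes); 60 patients (Study Design); 60 controls for interoception and 96 for the cognitive bias task (substudy 2 measures); two-sample t test (Data Analyses). No dropout allowance is stated for this calculation, and none is applied.

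**Formula.** Noncentral t with df = n1 + n2 − 2 and noncentrality ncp = d × √[n1·n2/(n1 + n2)]. Power is the probability that the statistic exceeds the critical value (in either tail, if two-sided).

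**Step 1: reproduce the stated figure.** For 51 versus 51, ncp = 0.5 × √(2601/102) = 0.5 × √25.5 = 2.525, with df = 100.
- One-sided .05: critical value 1.660, power 80.6%. At 50 per group the power is 79.9%. The exact solution is 50.15, which rounds up to 51. This is the stated number.
- Two-sided .05: critical value 1.984, power 70.6%. The stated number is not reproduced.

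The normal approximation agrees. One-sided, n = 2 × (1.645 + 0.842)² / 0.25 = 49.5, so 50 per group. Two-sided, n = 2 × (1.960 + 0.842)² / 0.25 = 62.8, so 63 per group.

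**Step 2: what two-sided .05 requires and delivers.**

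| Patients / controls | ncp at d = 0.5 | Two-sided power | Effect with 80% power |
|---|---|---|---|
| 51 / 51 | 2.525 | 70.6% | d = 0.56 |
| 60 / 60 | 0.5 × √30 = 2.739 | 77.5% | d = 0.52 |
| 64 / 64 | 0.5 × √32 = 2.828 | 80.1% | d = 0.50 |

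The exact two-sided solution is 63.8, so 64 per group. The normal approximation gives 71.4% at 51 per group and 78.2% at 60 per group. About 71% and about 78% are therefore fair summaries under either method.

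**Step 3: another possible origin of 51.** At two-sided .05 and the 60:100 allocation used for cognitive bias, the smaller group solves to 50.96, or 51. It must then be paired with 51 × 100/60 = 85 controls (power 80.0%). The article says 51 and 51, so this does not rescue the figure.

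**Step 4: nonparametric option.** If a rank test is used and its efficiency relative to the t test is taken as 0.955 (an assumption; the article gives no figure), two-sided power at 60 per group is about 76%.

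**Step 5: the cognitive bias figure, for comparison.** At 60/100, ncp = 0.5 × √37.5 = 3.062 and two-sided power is 86.1%. At 60/96, ncp = 0.5 × √36.92 = 3.038 and power is 85.5%. Both exceed 80%.

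**The case against.** **Sidedness is inferred.** The article never says one-sided or two-sided, and as a condensed account it may leave that to a fuller document. On this view 51 is a correct calculation under an unreported assumption. It is true that both sidednesses are inferences: one-sided from the exact match at 51, two-sided from the wording of the aims and analysis. But the complaint is not that a detail is missing. A power is stated that the comparison, as described, does not deliver.

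**A direction may have been intended.** The Discussion mentions inaccurate interoception and training accuracy through biofeedback, which hints at an expected deficit. Heightened sensitivity and poor accuracy are also different constructs, so the remark on hypersensitivity does not strictly contradict this. The adult studies behind the calculation may supply a direction, but they cannot be checked here. This stands to the extent that the text leaves direction unclear rather than ruling it out. It still contains no directional hypothesis to which a one-sided test could be tied.

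**The shortfall is small in practice.** This stands. The article calls 51 a minimum and plans 60 per group, where the gap is 2.5 points. Enrolment of children was also continuing while adolescents were still being recruited. By November 2024 there were 45 children, and the target was 30 adolescents. If 45 + 30 = 75 patients did the task against 60 controls, two-sided power would be about 82%. If the 12 patients of substudy 1 are part of that total and did not do it, 63 patients give about 79%. The article does not say how many will complete the task.

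**Stronger readings to avoid.** A reader might infer that the study's only powered comparison is underpowered. That is not so: the same paragraph also powers the cognitive bias comparison, which has about 86%. A reader might also take the 60 + 100 figure as a second error. It exceeds the stated 80% and harms nothing, and it rests on a different source study, so the article does not claim one method for both figures.

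**Conclusion.** The concern holds, at modest severity. As written, 51 patients and 51 controls do not give 80% power at d = 0.5 and α = .05 for the non-directional comparison that the article describes. They give about 71%, roughly 9 points less. At the planned 60 versus 60 the shortfall is about 2.5 points (77.5%), or equivalently an 80%-power effect of 0.52 instead of 0.50.

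This assumes a two-sided test at .05, a t test on a single outcome, and no loss of data. Use of a rank test would lower the figures slightly, and more patients completing the task would raise them. The design does not need to change, and the cognitive bias comparison is adequately powered.

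**What to change.** In Sample Sizes, state that the interoception calculation is two-sided, and correct it in one of two ways: give 64 per group as the size for 80% power at d = 0.5, or report that the planned 60 versus 60 has about 78% power at d = 0.5 and 80% at d = 0.52. When results are reported, recompute the power for the number of patients and controls who actually completed the heart rate discrimination task. If a one-sided test was intended, say so, justify the direction for each outcome, and make Data Analyses match.

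As a secondary edit, describe 60 patients with 100 (or the actual 96) controls for cognitive bias as giving about 86% two-sided power, since this is more than 80% power requires.

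The cost is wording only. No extra enrolment is needed; the one drawback is a slightly less favourable published figure for interoception.

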### Data Collection and Management

The DSQ, the BY-GIS task, and questionnaires are set up in REDCap (Research Electronic data capture; Vanderbilt University) [70], hosted by Aarhus University, and distributed through SMS text message or email. REDCap is a secure, web-based software platform designed to facilitate data capture for research studies.

For the DSQ (substudy 1), a text message reminder will automatically be sent through REDCap 2 hours after the initial SMS text message. If the DSQ is not completed 2 days in a row, a research assistant will contact the family by phone. For the BY-GIS task (substudy 2) and the extensive questionnaire (substudy 3), REDCap will generate automatic email reminders 24, 48, and 72 hours after the initial email if they are not completed. If there is no response after 7 days, a research assistant will contact the family by phone.

The interoception task in substudy 2 will take place at the Center of Functionally Integrative Neuroscience at Aarhus University Hospital in a behavioral testing room, and data will be stored in REDCap.

### Data Analyses

In substudy 1, visual inspection analyses will be applied to demonstrate the effect of the intervention on all outcomes [71]. In addition, within-case effect size measurements will be calculated using Tau-U [72] and between-case effect sizes will be determined using hierarchical linear regression models to account for the serial dependency of data [73]. A randomization test will be applied to test differences in means for the baseline versus treatment, and baseline versus follow-up periods, respectively [74].

In substudy 2, participants’ descriptions reported in the recall phase of the BY-GIS task will be coded to their corresponding word or picture and category presented in the encoding phase (eg, picture-description “children and cake” coded as the birthday picture within the fun category). Coding for the first 20% of participants will be conducted by 2 independent raters ([name] and [name]). If the consensus rating exceeds 90%, 1 rater will code the remaining cases independently. A third and experienced rater ([name]) may be consulted to resolve potential disagreements. Baseline data will be analyzed descriptively and compared with (1) data from a healthy control group who performed the same experimental test [38], and (2) end-of-treatment data, exploring potential differences in the outcomes from the encoding, recall, and recognition phases using *t* tests or nonparametric tests, depending on data variability in the samples.

Baseline measures of interoceptive performance and metacognitive measures will be analyzed descriptively and compared with (1) measures from a healthy control group and (2) end-of-treatment measures, using *t* tests or nonparametric tests, depending on data variability in the samples.

In substudy 3, the potential moderation of parental factors on treatment adherence (number of completed modules) and main measure (gastrointestinal symptoms) for children or adolescents will be investigated using negative binomial regression and linear mixed models, respectively, adjusting for baseline parental distress, illness worries, and illness behavior, respectively.

In addition, the potential effect of treatment on these parental factors and all other child or adolescent measures will be analyzed using linear mixed regression models.

An experienced statistician will provide statistical support for all analyses.

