### Measures

#### Measures in the Single Case Design Study (Substudy 1)

Children and adolescents will answer a daily short questionnaire (DSQ) throughout a pretreatment baseline period, randomized to last between 5 and 15 days, throughout the 10 weeks of treatment, and for a final 7-day follow-up period 3 months after treatment. The DSQ is an 8-item questionnaire, designed in line with the SCRIBE (Single-Case Reporting guideline In BEhavioural interventions) guidelines [32], addressing specific targets of the intervention, with items from different validated questionnaires for children and adolescents [32,33]. The full DSQ questionnaire is shown in Textbox 1. The primary outcome in the SCED study is the level of gastrointestinal symptoms assessed using 2 items from the Pediatric Quality of Life Inventory (PedsQL) Gastrointestinal Symptoms Questionnaire [34]. Secondary outcomes include illness worries, avoidance behavior, and level of pain acceptance as measured by the Visceral Sensitivity Index (VSI), irritable bowel syndrome behavioral response questionnaire (IBS-BRQ), and the Chronic Pain Acceptance Questionnaire – Adolescent Short Form (CPAQ-A8), respectively [35-37]. The items have been modified into questions concerning the last 24 hours and are rated on a 0-10 scale (“not at all” 0, “all the time” 10).

Daily short questionnaire (DSQ).During the last 24 hours, on a scale from 0 (not at all) to 10 (all the time)1) Did your stomach hurt?2) Did you feel discomfort in your stomach?3) Did you worry about the problems in your belly?4) Were you frightened when you felt discomfort in your belly?5) Did you avoid going out in case you had belly problems?6) Did you spent more time on the toilet than you ideally would like?7) Did you do things that are important and things that are fun even though you have problems in your belly?8) Has the most important thing been to keep your symptoms under control whenever you did something?

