The study has some limitations. In substudy 1, the generalizability of SCED study results has traditionally been questioned due to the low number of participants. However, our study adheres to guidelines that include multiple data points across different phases, randomization of the length of the baseline phase, and replication across several participants, thereby optimizing generalizability. Furthermore, participants are expected to answer daily questions for an extended period, which could induce some fatigue in responding and potentially affect reliability. Still, the inclusion of several close data points increases precision in analyses and helps buffer against occasional data loss. In addition, the setup was tested on 4 prestudy patients, who reported that the daily questionnaire was easy and quick to answer.

In substudy 2, we use the BY-GIS task, which is newly developed and has not been previously tested in patients. However, the task is developed based on well-known paradigms and previous tests, and it has already been tested in a sample of 96 healthy age-matched controls with good usability [38]. The interoception HRD measures participants’ ability to sense their pulse, which is not directly related to gut sensations but falls within the broader perspective of interoception. However, studies in adults suggest altered interoceptive accuracy across different diagnoses of functional disorders and chronic pain, which indicates that there may be a general hypersensitivity to inner sensations in this patient group as well [86]. Since this study is one of the first to investigate interoceptive accuracy in children and adolescents with FAPDs, we believe it is still valuable to use this well-known and widely used interoception measure.

Substudy 3 is an open pilot trial without a control group for comparison which means conclusions regarding the clinical effect of the treatment should be interpreted with caution. However, the substudy is explorative and primarily aims to investigate new and additional modifiable treatment targets on a parental level.

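### Substudy 1 randomizes only the baseline length, so it provides no design-based randomization test of baseline versus the 3-month follow-up

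*Protocol article*

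**What the plan says.** The protocol article describes one randomized element in substudy 1. Under Measures in the Single Case Design Study, daily ratings run through a "pretreatment baseline period, randomized to last between 5 and 15 days", then through 10 weeks of treatment, "and for a final 7-day follow-up period 3 months after treatment". The limitations paragraph under Principal Findings names the same element: "randomization of the length of the baseline phase". Sample Sizes explains where the reference set comes from: "The number of randomizations is influenced by both the number of participants and the number of possible starting points", and on that basis "we chose 6 participants in each group".

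Data Analyses then states: "A randomization test will be applied to test differences in means for the baseline versus treatment, and baseline versus follow-up periods, respectively". The same section also plans visual inspection, Tau-U within cases, and hierarchical linear regression for between-case effect sizes with allowance for serial dependency. No second randomization is described for the follow-up contrast, and neither the sidedness nor the significance level of the test is given.

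**The concern.** A randomization test compares the observed statistic with the values it would have taken under the other assignments that chance could have produced. In this design those assignments differ only in the day on which treatment starts. Moving the start day changes which early days count as baseline and which as treatment. It does not turn a follow-up day into a baseline day, or the reverse. The comparison of baseline with treatment therefore has a basis in the randomization, and the comparison of baseline with follow-up does not.

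At stake is the reading of the 3-month result on gastrointestinal symptoms, the primary outcome of the single-case study. A small p value could be reported as evidence of a sustained effect, or a large one as its absence, when the size of the change at follow-up had no bearing on either.

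**Working it through.** The article gives no power, significance level or p value for this test, so there is no stated figure to reproduce.

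**Inputs from the article**
- Baseline of 5 to 15 days. If every whole day is allowed (an assumption), that is 15 − 5 + 1 = 11 start points.
- Six participants per age group; 10 weeks = 70 treatment days; 7 follow-up days.
- Statistic: difference in means. Ratings run from 0 to 10, and lower is better for the symptom items.

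**Algebra**

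For participant i, let F_i be the mean of the 7 follow-up ratings and B_i(k) the mean of days 1 to k, with k from 5 to 15. The group statistic under start points k_1, ..., k_6 is

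T = Σ F_i − Σ B_i(k_i).

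The one-sided p value is the share of assignments with T no larger than the observed T. Σ F_i stands on both sides of that inequality and cancels. What remains is the share of assignments with Σ B_i(k_i) at least as large as the observed Σ B_i, which uses days 1-15 only. The argument is the same for a single case, for six cases or for all twelve.

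With |T| there are three situations:
- Follow-up below all the reference baseline means: p equals the one-sided p for improvement.
- Follow-up above all of them: p equals the one-sided p for worsening.
- Follow-up among them: p takes some other value.

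Within either of the first two situations p is constant, however far follow-up lies from baseline.

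**Enumeration**

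One simulated group of six, baseline near 6, all 11^6 = 1,771,561 assignments:

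| Follow-up level | One-sided p | p with absolute difference |
|---|---|---|
| 0 | 0.331821 | 0.3318 |
| 2 | 0.331821 | 0.3318 |
| 4 | 0.331821 | 0.3318 |
| 6 | 0.331821 | 0.8278 |
| 8 | 0.331821 | 0.6682 |
| 10 | 0.331821 | 0.6682 |

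The two outer values in the last column are complements (0.3318 + 0.6682 = 1.0000), as the algebra requires. A separate run on other simulated data showed the same pattern: 0.856 at levels 0-4 and 0.144 at levels 8-10.

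**Rejection rates**

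Assumed, because the article does not state them: one-sided level .05, daily SD 1.5, between-person SD 1, independent days. Each scenario had 1,500 simulated trials with 499 random reassignments per trial.

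| Scenario | Baseline vs follow-up, start points reassigned | Baseline vs treatment | Baseline joined to follow-up |
|---|---|---|---|
| No effect anywhere | 4.6% | 4.8% | 3.3% |
| No on-treatment effect, follow-up 4 points better | 4.4% | 4.7% | 99.9% |
| Immediate 3-point drop, full relapse at follow-up | 78.5% | 94.1% | 2.9% |
| Same drop, follow-up 4 points better | 79.7% | 94.4% | 99.9% |
| Same drop, follow-up 3 points worse than baseline | 78.4% | 94.1% | 0.0% |

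The first results column follows what happens early in treatment and ignores follow-up. It rejects after relapse because a reassigned baseline that is too long takes in improved treatment days, which makes the true baseline mean look high.

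**The case against.** The strongest reply is that the article names a contrast and a statistic but not the reassignment set for this contrast, and that such detail may sit in a fuller plan or in the cited method source, neither of which was available. An analyst could drop the treatment phase, join baseline to follow-up, and move the start point within that series. That version does respond to follow-up, so a reader who infers that no test under this name could respond goes further than the article supports. This part of the reply stands.

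It does not rescue the contrast. The joined version treats follow-up days as possible baseline days, which the stated randomization could never have made them. After a 5-day baseline the joined series has only 5 + 7 = 12 days, so baseline lengths of 12 to 15 leave no follow-up day at all. And 99.9% rejection with no on-treatment effect shows that it would reject equally for natural improvement over the intervening months.

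A second reply is that the article gives no direction, so a two-sided test is a natural reading. A reader might infer that p must be identical whether follow-up ratings are all 0 or all 10. That is true of the signed difference only; with an absolute difference p moved from 0.3318 to 0.6682.

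Third, follow-up is timed from the end of treatment, so another start day would have shifted its window by up to 15 − 5 = 10 days. Holding the observed block fixed is therefore a choice by the analyst. It still leaves no assignment that exchanges baseline with follow-up days.

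Finally, the main aim of substudy 1 is the detailed trajectory of effect, several other analyses are planned, and the test of baseline versus treatment is sound. This limits the reach of the point to one contrast.

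**Conclusion.** The point holds for baseline versus follow-up and for nothing else in substudy 1. The randomization of baseline length gives no design-based test of the 3-month change. Under start-point reassignment with the follow-up block as observed, the one-sided p value is exactly unaffected by the follow-up ratings. With an absolute difference it can reflect the side of baseline on which follow-up falls, or that it lies among the baseline means, but not how large the change is. The joined version responds but is not justified by the randomization.

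The cancellation is algebra and rests on no assumed variance. The rejection rates, about 4% despite a 4-point benefit and about 78% despite relapse or worsening, depend on the assumed SDs, independent days and one-sided .05 level, and are illustrations. The 11 start points assume that every whole day was allowed.

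**What to change.** - Keep the randomization test for baseline versus treatment, and drop it for baseline versus follow-up.
- Estimate baseline versus follow-up by adding a follow-up phase term to the hierarchical regression named under Data Analyses, allowing for serial dependency. The article plans that model for between-case effect sizes but states no such term, so this is an addition.
- Optionally, add a sign-flip test on the case-level differences within each group of six. Its smallest two-sided p is 2/2^6 = 2/64 = 0.031, and it assumes that the differences are symmetric about zero under the null hypothesis.
- Label the result a non-randomized before-after contrast.

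No new data are needed. The cost is a short change to the analysis text and one further model term. The Results section says that substudy 1 is finalized, so the change should be disclosed in the report, with its reason, as a departure from the published plan.
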